## Discussion

Monitoring of illness activity using smartphones seems promising as an intervention in unipolar disorder and bipolar disorder, but few studies using rigorous methodology have been published. No study investigating the effect of a smartphone-based intervention on rate and duration of re-admissions in both unipolar disorder and bipolar disorder has been published. The RADMIS trials aim to investigate the effect of a smartphone-based monitoring and treatment system on the risk of psychiatric hospitalization, clinical function, and wellbeing in randomized, controlled trials with clearly defined clinical outcome measures.

### Advantages

First, the RADMIS trials’ use a pragmatic design with few exclusion criteria and the results of the trials will be generalizable to patients who are going to be discharged from psychiatric hospitals in general with a diagnosis of unipolar disorder or bipolar disorder and have clinical relevance. The patients are recruited at a critical time point at discharge from hospital at which they still suffer from some affective symptoms and have a need for continued treatment. Following hospitalization, patients often experience a service gap between inpatient and outpatient services, and the RADMIS smartphone-based monitoring and treatment system is developed among others to fill out this gap.

Second, it is a major advantage that clinical information on the primary outcome will be available for all included patients (100%), regardless of whether they drop out of the RADMIS trials or not, as data on date of re-admission and duration of re-hospitalizations routinely are reported nationwide to the Danish Psychiatric Central Register [40]. Also, the information on re-admissions and duration of re-hospitalizations are collected without the risk of unblinding of the researcher and not based on the patients’ subjective evaluations.

Third, information on the secondary outcome measures are based on standardized clinical rating scales often used as the “gold standard,” and are conducted by trained researchers blinded to intervention groups. In contrast to this, the tertiary outcomes are based on the patients’ subjective and unblinded evaluations and are, thus, at risk of performance bias.

Fourth, the intervention used in the RADMIS trials is specifically designed to address the needs of the patients when being discharged from a psychiatric hospitalization. During the design phase of the trial the software was designed in a close collaboration between patients with unipolar disorder and bipolar disorder, IT researchers, clinicians, and clinical researchers during an interactive process.

Fifth, automatically generated behavioral data collected by the smartphones will be combined in an aggregated combined measure of illness activity that will be reported as an additional outcome measure. These data are objective and have been shown to correlate with the severity of depressive and manic symptoms in studies by our group. However, using these data as outcome measures is still experimental and will be developed further during the RADMIS trials. Consequently, the aggregated smartphone-based measure of illness activity is not included as a predefined outcome measure in this study protocol.

Sixth, the Monsenso system will be available for both Android and iPhones. Thus, patients are not excluded due to preference of smartphone type and/or operating system. Patients randomized to the intervention group are offered to loan a smartphone free of charge during the RADMIS trials and, thus, there are no requirements for smartphone access.

### Limitations

#### The intervention group

The RADMIS trials are designed to investigate the effect of the entire Monsenso system, including self-monitoring, automatically generated behavioral data, integrated feedback loop and context-aware CBT modules. Thus, we will not be able to distinguish the effects of the individual components of the intervention.

However, in subanalyses it will be investigated whether there are differences in outcome measures between patients who have used the CBT modules during the trial period and patients who have not.

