### Study procedure

Potential participants are invited to participate in the RADMIS trials by contact with the staff during hospitalization. All potential participants who accept to meet with the RADMIS staff for further trial information are screened by trained researcher to make sure that they fulfil the criteria for participation, and are then included in the RADMIS trials. Following inclusion, baseline assessments are performed on all patients, and after these assessments the numbered opaque allocation envelopes are distributed by a research secretary ([name]) to the RADMIS study nurses. The included patients are randomized separately according to psychiatric diagnosis (unipolar disorder or bipolar disorder) to either the intervention group or the control group for a 6-month trial period.

An overview of the outcome assessments conducted by researchers blinded to intervention group is presented in Table 1. Information regarding the primary outcome, re-admissions and duration of re-admissions, will be obtained after completion of the two RCTs by linkage of the unique personal identification number (CPR) which is assigned to all 5.4 million persons living in Denmark [39] with the Danish Psychiatric Central Register [40].

**Table 1 Tab1:** Outcome assessments during the RADMIS trial

	SCAN and background information	Rating scales	Questionnaires	Clinical information
Baseline	x	x	x	x
Randomization to (1) smartphone-based monitoring and treatment (the intervention group) or (2) treatment-as-usual (the control group)				
3-month follow-up		x	x	x
6-month follow-up		x	x	x

*SCAN* Schedules for Clinical Assessment in Neuropsychiatry interview

Rating scales: Hamilton Depression Rating Scale 17-item (HDRS-17); Young Mania Rating Scale (only for patients with a bipolar disorder diagnosis); Psychosocial functioning test (Functional Assessment Short Test (FAST))

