##### Smartphone-based CBT modules

The smartphone-based CBT modules include four modules: psychoeducation, behavioral activation, cognitive restructuring and rumination-focused CBT. The psychoeducation and mood-monitoring system include strategies for detecting and intervening with early signs of relapse. Patients are encouraged to use the module in an individualized and sequential way according to their condition, affective state, and insight and following guidance from the study nurse if wanted. The behavioral activation module was inspired by Martell et al. (2010) and Lejuez et al. (2001) [41, 42]. It includes activity monitoring and activity scheduling and focus on regulation of sleep and daily routines. Several studies have established the efficacy for behavioral activation for treating depression [43–46] including a few studies of behavioral activation using smartphones; however, not including a control standard treatment arm [47, 48]. Further, regulating patterns of activity and sleep are helpful in reducing both depressive and manic symptoms [43, 49].

The cognitive restructuring includes simple techniques to help patients to identify and modify dysfunctional automatic thoughts. Cognitive restructuring is a key element of CBT and is included in a number of studies that show the efficiency of CBT in the treatment of depression including some studies of Internet-based CBT [50, 51], and a few studies including patients with bipolar disorder [20, 22].

A main purpose of the smartphone-based CBT modules was to help patients to reduce depressive ruminations. Therefore, a specific rumination-focused CBT strategy, based on the theory and practice described by Watkins et al. [25], was included. Rumination-focused CBT has shown encouraging results in the treatment of residual depression [25] and the Monsenso system includes the identification and reduction of unhelpful ruminations.

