### Statistical power and sample size calculation

The statistical power and sample size was calculated using http://stat.ubc.ca/~rollin/stats/ssize/n2.html.

The primary outcomes are differences in the number and duration of re-admissions to a psychiatric hospital between the intervention group and the control group − analyzed separately according to psychiatric diagnosis (unipolar disorder or bipolar disorder). Power calculations are similar for the two RCTs/patient groups (unipolar disorder or bipolar disorder). Based on prior findings aiming to reduce re-hospitalization due to recurrent depression [66] and bipolar disorder [9], combined with presumptions of positive effects of the immediate early contact with patients during the vulnerable period following discharge from a psychiatric hospital, regardless of diagnosis, we expect a reduction in re-admissions from 30% to 15% in the intervention group using smartphone-based treatment. Thus, anticipating a hazard ratio (HR) of 0.50 in the comparison of the intervention group with the control group on the primary outcome, a two-sided risk of type 1 error, *α* of 0.05, a type 2 error risk, *β*, a statistical power of 80%, the sample size (*N*) is calculated as *N* = 200 (100 patients in each arm of each RCT) per RCT and, thus, a total of 400 patients (200 patients with unipolar disorder and 200 patients with bipolar disorder) is estimated to be required for the RADMIS trial. Cumulated durations of re-hospitalizations comprise similar power calculations and sample sizes. Regarding the secondary outcomes, the clinically relevant difference in depressive or manic symptoms is defined as a minimum of three scores on the HDRS-17 or on the YMRS, respectively, and the standard deviation (SD) is set at 7 with a mean score of 12 versus 15 in the intervention group and the control group, respectively. The statistical power to detect a three-score difference in the areas under the curves between the intervention and the control groups on the HDRS-17 or the YMRS, respectively, is 80% with *α* = 0.05 for a two-sample comparison of means including a total of 200 patients (100 patients in each arm) in each of the two RADMIS RCTs.

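### The user versus non-user comparison of the CBT modules classifies patients over the same six months in which re-admission is counted, so it is open to immortal-time bias and confounding of unknown size

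*Protocol article*

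**What the plan says.** In the Discussion, under Limitations (The intervention group), the protocol article first concedes that "we will not be able to distinguish the effects of the individual components of the intervention". It then offers a partial way round this: subanalyses will examine "whether there are differences in outcome measures between patients who have used the CBT modules during the trial period and patients who have not". The grouping is ever use against never use, and the window is the whole trial period. The outcomes are not restricted, so the primary ones (rate and duration of re-admission) are included. Nothing there says whether control patients count as non-users; I read the comparison as one within the intervention arm.

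Uptake is left to the patient. Under Smartphone-based CBT modules the article states: "Patients are encouraged to use the module in an individualized and sequential way according to their condition, affective state, and insight". It gives no common start date, no expected uptake and no minimum amount of use.

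**The concern.** Randomisation does not protect this comparison, because module use is behaviour that follows it. Two separate problems arise.

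- **Timing.** To become a user, a patient must reach the day of first use. If re-admission stops or postpones that day, users carry a stretch of follow-up that is free of re-admission by construction, and patients re-admitted early collect among the non-users. This is immortal-time bias, and it favours the module.
- **Confounding.** Use depends on condition and insight, so users and non-users differ in prognosis. Patients who turn to the modules because they are getting worse would make the modules look harmful; patients with better insight or function would make them look helpful.

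At stake is how one exploratory result is read: the CBT component could be credited with preventing re-admission when it does nothing. The caveat beside it in the article mentions neither problem.

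**Working it through.** The plan gives no figure for this subanalysis, so there is none to reproduce. The check asks what an ever/never comparison would show if the modules did nothing.

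**Inputs from the article.** Follow-up is 26 weeks, from the trial period: "to either the intervention group or the control group for a 6-month trial period". Re-admission risk in the intervention arm is p = 0.15, from the sample-size section: "we expect a reduction in re-admissions from 30% to 15% in the intervention group using smartphone-based treatment".

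**Assumptions, none of them in the article.** Uptake is 50%; time to first use is independent of prognosis; the re-admission hazard is constant. The timing of first use, and whether re-admission blocks it, are varied.

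**Case A: uptake at a constant rate over six months, re-admission always blocks first use.** With six months as the time unit, the re-admission rate is λ = −ln(0.85) = 0.1625 and the uptake rate is μ = −ln(0.50) = 0.6931.

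- P(user) = μ/(μ+λ) × [1 − exp(−(μ+λ))] = 0.8101 × (1 − 0.425) = 0.4658
- P(user, not re-admitted) = 0.50 × 0.85 = 0.4250
- P(user, re-admitted) = 0.4658 − 0.4250 = 0.0408
- Risk in users = 0.0408/0.4658 = 8.8%
- Risk in non-users = (0.15 − 0.0408)/(1 − 0.4658) = 20.4%
- Apparent risk ratio = **0.43**, where the truth is 1

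**Case B: half of the blocked patients still start after re-admission.** Blocked patients make up 0.50 × 0.15 − 0.0408 = 0.0342 of the arm; half is 0.0171.

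- Risk in users = (0.0408 + 0.0171)/(0.4658 + 0.0171) = 12.0%
- Risk in non-users = (0.15 − 0.0579)/(1 − 0.4829) = 17.8%
- Apparent risk ratio = **0.67** (a simulation of 600,000 patients gave 0.68)

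**Case C: early first use, full blocking.** Among would-be users, first use is exponential with mean m weeks. The weekly re-admission hazard is h = 0.1625/26 = 0.00625, and the share blocked is h/(h + 1/m), ignoring the negligible tail beyond week 26.

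| Mean start | Share blocked | P(user) | Risk, users | Risk, non-users | Risk ratio |
|---|---|---|---|---|---|
| 1 week | 0.0062 | 0.497 | 14.5% | 15.5% | **0.93** |
| 2 weeks | 0.0123 | 0.494 | 13.9% | 16.0% | **0.87** |
| 4 weeks | 0.0244 | 0.488 | 12.9% | 17.0% | **0.76** |

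If the re-admission hazard is front-loaded (Weibull shape 0.6), the four-week row falls to 0.59 in simulation. The Background describes the time after discharge as high-risk, but gives no curve.

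**Case D: re-admission never prevents first use.** Both groups have 15% risk, and the ratio is **1.00**.

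Across all scenarios simulated (uptake 20% to 90%, risk 15% or 30%, both hazard shapes, several start patterns) the ratio ran from about 0.11 to 1.0.

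**Check of the remedy.** For the same inert module at 50% uptake and 15% risk, a week-4 landmark gave a risk ratio of 1.00, and use as a time-dependent exposure gave a rate ratio of 0.99. Both agree with the true value of 1.

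**The case against.** A reader might infer that an inert module would appear to more than halve re-admissions. The documents do not support this. A ratio below 0.5 needs late or spread-out uptake, or high uptake with front-loaded risk, together with re-admission blocking first use in most or all cases. Early opening is plausible, since one module is psychoeducation and nurse guidance is available; with constant hazard it gives 0.76 to 0.93 at 50% uptake.

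Nor does an early re-admission by itself make a patient a non-user. Statistical methods says data are collected until dropout or the end of the trial period, and nothing says that module access stops at re-admission. A patient re-admitted in week 2 who opens a module in week 8 is a user under the stated rule.

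The net direction is also open, because use driven by worsening condition could offset or reverse the timing bias. The timing argument does not carry over directly to rating scales and questionnaires taken at scheduled assessments; the confounding does.

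Finally, this is one sentence under Limitations. Component effects appear in none of the hypotheses, objectives, outcome lists or statistical methods, so they cannot be called a main aim, and model details may sit in an analysis plan that is not shown.

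These points limit the size and weight of the concern but do not remove it. The article does more than leave details open: it states the grouping and its window, and for re-admission that rule can give a wrong answer.

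**Conclusion.** The point stands in a limited form. As stated, the comparison is open to immortal-time bias for the re-admission outcomes and to confounding for all outcomes. At 15% risk and 50% uptake, timing alone moves the risk ratio of an inert module to anywhere between about 0.43 and 1.0 in the constant-hazard cases A to D, depending on when patients first use a module and whether re-admission stops them. Uptake, timing and blocking are all assumptions. The randomised comparisons, the sample size and the primary conclusions are not touched. This is an inexpensive improvement to one exploratory subanalysis.

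**What to change.** For re-admission, use one of two definitions:

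- **Landmark.** Classify patients by any module use in, for example, the first 4 weeks after randomisation, and analyse only later events in patients not yet re-admitted.
- **Time-varying use.** Enter module use in a Cox model as a covariate that switches on at first use.

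For all outcomes, adjust for baseline HDRS-17 (and YMRS in the bipolar trial) and for prior hospitalisations, state whether control patients are included, and report the result as exploratory and non-randomised.

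The cost is a sentence or two. The landmark drops earlier re-admissions from this subanalysis and counts later starters as non-users. Either option needs the date of first module use, which the article does not say is recorded. Both remove the timing bias; baseline adjustment reduces confounding but cannot remove it, because use follows the patient's changing condition.

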#### The control group

It is always difficult to define a proper control group. In a previously trial conducted by the authors, an effect of a “placebo smartphone” was most likely not found [32]. Further, during the last years few of the patients participating in our studies have expressed a wish to loan a smartphone free of charge. Thus, we chose not to offer a placebo smartphone in the present RADMIS trial.

#### Secondary and tertiary outcome measures

The secondary outcome measures are differences in clinically rated depressive and manic symptoms as assessed with standardized rating scales. Since the patients are aware of their allocation status these outcome measures are single blinded. The tertiary outcomes are questionnaires evaluated by the patients themselves and are, therefore, unblinded.

### Perspectives

If the Monsenso system proves effective in reducing the rate and duration of re-admissions in patients with unipolar disorder and bipolar disorder in the present trial, there will be basis for using a system of this kind in psychiatric treatment in general and on a larger scale.

### Trial status

The trial is ongoing. Recruitment begins March 2017.

## Abbreviations

ASRM: The Altman Self-rating Scale for Mania
BDI: Beck’s Depressive Inventory
CBT: Cognitive behavioral psychotherapy
FAST: The Functional Assessment Short Test
HDRS-17: The Hamilton Depression Rating Scale 17-item
HDRS-6: The Hamilton Depression Self-rating Scale 6-item
HR: Hazard ratio
ITT: Intention-to-treat
PSWQ: The Penn State Worry Questionnaire
RCT: Randomized controlled trial
RRS: The Ruminative Response Scale
SCAN: Schedules for Clinical Assessments in Neuropsychiatry
The MONARCA system: Smartphone-based monitoring system for patients with bipolar disorder
The Monsenso system: Smartphone-based monitoring system including CBT modules for patients with both unipolar disorder and bipolar disorder (inspired by the MONARCA system)
The RADMIS trial: Reducing the rate and duration of Re-ADMISsions among patients with unipolar disorder and bipolar disorder using smartphone-based monitoring and treatment
VSS-A: The Verona Satisfaction Scale-Affective Disorder
WHOQOL-BREF: The WHO Quality of Life-BREF
YMRS: The Young Mania Rating Scale
